### Aims and Contributions

In this study, we propose a robust “in-the-wild” evaluation of our novel technology tool by the platform’s intended users—PRCs and their clients—to assess its usability and its impact on specific client-centered recovery outcomes. Based on the findings of this real-world testing, we will subsequently refine the platform design and develop an implementation tool kit for future deployment. Specific study aims are displayed in Table 2.

**Table 2. T2:** Aims and milestones to be accomplished by the end of the R21 study period.

Aims and objectives	Milestone
Aim 1: Determine if Peer PLUS^a^ is perceived as usable and has sustained use by PRCs^b^ and their clients.	
Refine: Apply UCD^c^ methods and RE-AIM^d^ [38] to refine Peer PLUS and develop an implementation tool kit.	Revised Peer PLUS app Draft implementation tool kit
Usability and feasibility: Validate that Peer PLUS is easy to use and determine if it is likely to have uptake and sustained use in the proposed R33 phase.	Clients and PRCs evaluate Peer PLUS with an average SUS^e^ [44] ≥68 25% of clients approached to participate in the pilot will have a smartphone and consent to participate PRCs connect to clients who are using Peer PLUS 20% more than clients who are not
Aim 2: Evaluate the potential impact of Peer PLUS on recovery, quality of care, and therapeutic alliance between clients and their peer recovery coach during care for SUD^f^.	
Impact: Demonstrate Peer PLUS impact and ability to robustly evaluate the app in the proposed R33 phase.	The following metrics are collected from all clients participating in the pilot SURE^g^ [45] CAHPS^h^ ECHO^i^ [40] WAI-SR^j^ [46,47]

a PLUS: People Leveraging Urgent Support.

b PRC: peer recovery coach.

c UCD: user-centered design.

d RE-AIM: Reach, Effectiveness, Adoption, Implementation, and Maintenance.

e SUS: System Usability Scale.

f SUD: substance use disorder.

g SURE: Substance Use Recovery Evaluator.

h CAHPS: Consumer Assessment of Healthcare Providers and Systems.

i ECHO: Experience of Care and Health Outcomes.

j WAI-SR: Working Alliance Inventory.

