## Methods

### Feasibility Objectives and Outcome Measures

This work constitutes the first phase (R21; 2 years) of a 5-year federal research grant from the Agency for Healthcare Research and Quality (AHRQ) to test Peer PLUS, develop an implementation tool kit, and determine whether the tool has sufficient usability and impact to move to the final phase of the grant (R33; randomized clinical trial). The study aims and associated objectives and outcome measures for the present phase are summarized in Table 2.

To accomplish these objectives, in year 1, we will conduct a series of UCD activities, refine the platform, and deploy it with a small sample during beta testing. In year 2, we will continue UCD work, complete further refinement, develop an implementation tool kit, and conduct a pilot study.

For aim 1, we will use UCD methods to refine the functionality of Peer PLUS (eg, develop new features) and apply implementation science frameworks to develop an implementation tool kit. We will validate usability with the 10-item System Usability Scale (SUS) [44] and our own custom user experience survey incorporating RE-AIM elements. We will also measure frequency of use through app interaction logs as a proxy to determine likelihood of sustained use in the proposed R33 phase. Primary outcome measures for the pilot study will include usability ratings (SUS score ≥68; ie, above average) and app usage statistics (20% more connections to clients using the app, compared to contacts with nonparticipating clients, which is documented as standard of care). Based on the client population of the health system, we will target 25% as the proportion of clients approached who are eligible and consent to determine the feasibility of recruiting the target sample size (n=200) for the trial proposed in the R33 phase.

In aim 2, we will assess the platform’s impact on clients through several validated instruments, including the Substance Use Recovery Evaluator (SURE) [45] to assess recovery, the Consumer Assessment of Healthcare Providers and Systems (CAHPS) Experience of Care and Health Outcomes (ECHO) [48] to assess experience with receiving PRC services, and the WAI-SR [46,47] to assess therapeutic alliance. This will demonstrate the ability to robustly evaluate the app in the proposed R33 trial.

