**Client: inclusion criteria**
Has a substance use disorder (SUD) diagnosisReceives SUD support from a peer recovery coach (PRC)Has access to a functioning Android or Apple smartphone with the ability to receive and send textsFor clients with Android smartphones only, must have a Gmail account or be willing to set up a Gmail accountAble to download apps from their smartphone’s app storeHas an accessible email address or is willing to set up an email accountPer PRC’s professional judgment, is an appropriate candidate to participate in the study

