**Client: exclusion criteria (pilot only)**
Has been engaged in the program for more than 6 months

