#### Eligibility Criteria

Study participants were included based on the criteria listed in Textbox 2. In this study, PRCs were employed by the health system of the study, although their clients may not be patients of that health system, as they may have been referred through another pathway. This participant population is appropriate for the subject of study due to their status as intended real-world users of the mobile app engaged in a peer support relationship. For the pilot test in particular, we updated the criteria to exclude clients who had been engaged in the peer recovery program for more than 6 months, based on feedback from initial beta test participants regarding the specific utility of the Peer PLUS platform in building the PRC-client relationship and introducing new resources during the early stages of treatment.

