#### Pilot Phase

In the pilot phase, we will seek to enroll PRCs in a more naturalistic manner. As such, the study team will obtain a list of all currently employed PRCs from the manager and contact them to assess interest. Once enrolled, their clients will form the pool of eligible participants. The trust between the PRC and the client is key. Thus, a purely naturalistic recruitment strategy for clients is not feasible, as we wanted to ensure that trust in the program had been developed before approaching newer clients to participate in the study, and we did not want to disrupt the health system’s existing processes for engaging clients in the program. The study team will provide recruitment flyers and training on inclusion and exclusion criteria to PRCs so that they can introduce the study to their clients. If an eligible client expresses interest, the PRC will check “Yes” in the “informed about study” section in the client management system. The study team will run reports to identify which clients have been informed about the study and thus need to be contacted for recruitment. For all recruitment activities, participants may be initially contacted by phone and/or email (and/or Microsoft Teams, in the case of PRCs). Institutional review board (IRB)–approved scripts for emails and calls will be used but may be adapted as necessary for clarity and/or to answer participant questions or concerns.

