### Statistical Analysis Plan

Data will be analyzed at the aggregate level. To address aim 1 (usability and potential for sustained use), descriptive statistics will be computed on the SUS and recruitment rates to assess whether feasibility targets are met (ie, SUS score ≥68, 25% client eligibility and recruitment rate). Using data collected from the Peer PLUS user log, we will conduct a general categorical analysis as a proxy for end-user engagement. To assess our primary outcome related to client contact, in the pilot trial, we will compare the number and rate of connections to clients using the platform to PRCs’ documentation of contact with nonparticipating clients to determine whether the target of 20% more contacts with enrolled clients was met. Further, to address aim 2 (evaluating the impact of Peer PLUS on treatment-related outcomes), descriptive statistics will be calculated for the SURE, CAHPS ECHO, and WAI-SR survey measures deployed during the pilot trial, which will demonstrate potential improvement related to recovery, quality of care, and therapeutic alliance, as well as the feasibility of using these measures to evaluate the app in the R33 phase.

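### The 20% contact milestone compares selected, early-stage enrolled clients with nonparticipating clients to whom none of the same limits applies, so program stage and selection alone could produce or mask the difference

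*Protocol article*

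**What the plan says.** Table 2 (Aims and Contributions) lists the milestone "PRCs connect to clients who are using Peer PLUS 20% more than clients who are not". Feasibility Objectives and Outcome Measures makes it a primary pilot outcome: "20% more connections to clients using the app, compared to contacts with nonparticipating clients, which is documented as standard of care". The Statistical Analysis Plan section describes the comparison: "we will compare the number and rate of connections to clients using the platform to PRCs’ documentation of contact with nonparticipating clients", in order to "determine whether the target of 20% more contacts with enrolled clients was met". None of the three places restricts the comparator, and none mentions matching, stratification or a baseline period.

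Enrolled pilot clients are restricted in several ways:

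- **Program stage.** Textbox 2 excludes from the pilot any client who "Has been engaged in the program for more than 6 months". Eligibility Criteria explains that beta participants saw the platform's value in "building the PRC-client relationship and introducing new resources during the early stages of treatment".
- **Phone and endorsement.** Textbox 2 requires access to a working smartphone and that the client, in the PRC's "professional judgment, is an appropriate candidate to participate in the study".
- **Interest and trust.** Under Recruitment Methods, Pilot Phase, a client is flagged for contact only "If an eligible client expresses interest", and newer clients are approached only after trust in the program has formed.
- **PRC.** Overview of Study Design requires that the client's own PRC is enrolled.

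The nonparticipant data named in Table 4 are demographic examples (race, ethnicity, age group), plus the reason for declining. The Limitations section does not mention that the two groups differ by construction.

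**The concern.** A contact ratio is informative about the app only if the two groups would have had similar contact without it. Here they differ in program stage, phone access, PRC endorsement, interest and possibly PRC. Any of these could move the contact rate. The 6-month limit was added for the pilot because the early period is when the relationship is built, so the article itself treats stage as relevant to PRC-client interaction. Yet the comparator carries no matching limit.

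The ratio can also rise if an enrolled PRC moves time from nonparticipating to participating clients, with no gain overall.

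The milestone is one of those behind the R33 go/no-go decision in Table 3. A ratio that stage and selection can push either way may signal sustained use where there is none, or hide it where it exists.

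**Working it through.** There is no plan figure to reproduce. The 20% is a set target, given without a contact rate, spread or derivation. The check asks what ratio the stated comparison would show if the app did nothing.

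**Inputs from the article.** Target ratio 1.20 (Table 2); enrolled clients at 6 months or less at entry (Textbox 2); use of up to 6 months (Intervention; Overview of Study Design); comparator unrestricted (Statistical Analysis Plan).

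**Assumed inputs, not in the article.** p = share of the comparator beyond 6 months; r = their contact rate relative to early-stage clients; s = extra contact among endorsed, interested, smartphone-equipped clients; q = share of enrolled follow-up that falls beyond month 6.

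**1. Stage only (s = 1, q = 0).** Set the early-stage rate to 1. The comparator rate is (1 − p) + pr = 1 − p(1 − r), so the null ratio is 1/(1 − p(1 − r)). It reaches 1.20 when 1 − p(1 − r) = 1/1.20, that is, p(1 − r) = 1/6.

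| p | r | 1 − p(1 − r) | Null ratio |
|---|---|---|---|
| 0.5 | 2/3 | 0.833 | 1.20 |
| 0.5 | 0.5 | 0.750 | 1.33 |
| 0.7 | 0.5 | 0.650 | 1.54 |
| 0.3 | 0.8 | 0.940 | 1.06 |

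**2. The opposite direction.** If later clients are contacted more often, say r = 1.25 with p = 0.5, the null ratio is 1/1.125 = 0.89. A true app ratio of 1.20 would then appear as 1.20 × 0.89 = 1.07, and the target would be missed.

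**3. Enrolled follow-up past month 6.** The limit applies at entry, so a client entering at month m and followed for 6 months has q = m/6. The ratio becomes (1 − q(1 − r))/(1 − p(1 − r)).

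- At p = 0.5, r = 0.5: entry at month 1.5 (q = 0.25) gives 0.875/0.750 = 1.17; entry at month 3 (q = 0.5) gives 0.750/0.750 = 1.00.
- At p = 0.7, r = 0.5: the same entries give 0.875/0.650 = 1.35 and 0.750/0.650 = 1.15.

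The table in step 1 is therefore an upper bound for each pair with r below 1.

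**4. Selection.** The step 1 ratio is multiplied by s. With s = 1.1, p = 0.5 and r = 0.8 it is 1.1/0.9 = 1.22. With s = 1.2 and no stage difference it is 1.20.

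**5. Displacement.** If contact with enrolled clients is unchanged and contact with nonparticipants falls by one-sixth, the ratio is 1/(5/6) = 1.20.

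**6. After aligning stage.** With the same stage mix in both groups, p and r cancel and the null ratio is s. That is 1.00 without further selection, but still 1.10 or 1.20 if s is 1.1 or 1.2. Aligning stage is necessary but not sufficient.

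**The case against.** The sponsor has a fair reply on several points.

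- **Stakes.** Table 2 files the target under usability and feasibility, and Feasibility Objectives and Outcome Measures treats frequency of use as a proxy for sustained use. The next step is a randomized trial against a control app, with the SURE recovery scale as primary outcome. A reader might infer that a wrong go would amount to an efficacy claim or lead to adoption. The article does not support that, because a go leads to a randomized test. The target is still a primary pilot outcome and feeds that decision.
- **Who is in the comparator.** A reader might infer that it comprises every nonparticipating client, including clients of PRCs who did not enrol. The text does not say so. It is unqualified, and the Table 2 wording can be read as a comparison within the same PRCs. The gap is that none of the three statements settles this.
- **Direction.** A reader might infer that the bias must favour the app. No section gives contact rates by stage, and Eligibility Criteria does not say that contact falls after 6 months. Clients without phones or judged unsuitable might need more contact.
- **Level of detail.** Matching rules are often left to a full analysis plan. But the article's own Statistical Analysis Plan section names the comparison, and what it names is not aligned with the pilot eligibility criteria.

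**Conclusion.** The point stands. As written, the comparison sets a group selected on program stage, phone access, PRC endorsement, interest and PRC enrolment against a group to which none of these limits is applied. A ratio of 1.20 can then be met or missed for reasons other than the app.

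The size is not known. Under the assumed inputs, stage alone gives null ratios from 0.89 to 1.54, and enrolled follow-up past month 6 pulls the higher values down, to 1.00 in one case shown. Selection of 1.2 meets the target by itself. These results show that the milestone cannot separate an app effect from stage and selection. They do not show that it will be met falsely, nor that the bias runs one way.

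**What to change.** In Table 2, Feasibility Objectives and Outcome Measures, and the Statistical Analysis Plan section:

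- Define the comparator as nonparticipating clients of the same enrolled PRCs who were 6 months or less in the program at a matched index date, followed over the same calendar window and months since program entry.
- Restrict it to clients with an eligible smartphone where this is recorded.
- Compute the contact rate ratio within PRC from the client management system. Table 1 shows that it holds encounter data and the attached coach, and Results says it is now used across the whole PRC team.
- Report the nonparticipant contact rate before and during the pilot, so that displacement of PRC time is visible.
- Use pre-enrolment contact rates only as a sensitivity analysis where history exists. Clients enrolled soon after program entry have too little history for a before-after change to be the main estimate.
- State that selection by PRC judgment and client interest remains, so the milestone shows association and not an app effect.

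No new participants or visits are needed. The cost is fewer comparator clients and a wider interval. An IRB wording change may also be needed, because the nonidentifying extract would have to carry months in program, PRC and contact counts.

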## Methods

### Feasibility Objectives and Outcome Measures

This work constitutes the first phase (R21; 2 years) of a 5-year federal research grant from the Agency for Healthcare Research and Quality (AHRQ) to test Peer PLUS, develop an implementation tool kit, and determine whether the tool has sufficient usability and impact to move to the final phase of the grant (R33; randomized clinical trial). The study aims and associated objectives and outcome measures for the present phase are summarized in Table 2.

To accomplish these objectives, in year 1, we will conduct a series of UCD activities, refine the platform, and deploy it with a small sample during beta testing. In year 2, we will continue UCD work, complete further refinement, develop an implementation tool kit, and conduct a pilot study.

For aim 1, we will use UCD methods to refine the functionality of Peer PLUS (eg, develop new features) and apply implementation science frameworks to develop an implementation tool kit. We will validate usability with the 10-item System Usability Scale (SUS) [44] and our own custom user experience survey incorporating RE-AIM elements. We will also measure frequency of use through app interaction logs as a proxy to determine likelihood of sustained use in the proposed R33 phase. Primary outcome measures for the pilot study will include usability ratings (SUS score ≥68; ie, above average) and app usage statistics (20% more connections to clients using the app, compared to contacts with nonparticipating clients, which is documented as standard of care). Based on the client population of the health system, we will target 25% as the proportion of clients approached who are eligible and consent to determine the feasibility of recruiting the target sample size (n=200) for the trial proposed in the R33 phase.

In aim 2, we will assess the platform’s impact on clients through several validated instruments, including the Substance Use Recovery Evaluator (SURE) [45] to assess recovery, the Consumer Assessment of Healthcare Providers and Systems (CAHPS) Experience of Care and Health Outcomes (ECHO) [48] to assess experience with receiving PRC services, and the WAI-SR [46,47] to assess therapeutic alliance. This will demonstrate the ability to robustly evaluate the app in the proposed R33 trial.

### Setting

The study is being conducted within a mid-sized not-for-profit learning health system in the Midwestern United States. The system serves an area with significant need for SUD support and has a robust network of existing treatment pathways, including the largest behavioral health hospital and medication-assisted treatment (MAT) facilities in the region, and has employed PRCs for more than 8 years. The multidisciplinary study team is based at the health system’s embedded Center for Research and Innovation and has prior experience creating digital solutions to support clients while maintaining health information privacy. The team includes researchers specializing in UCD, human-computer interaction, health technologies, clinical psychology, and addiction recovery, including peer recovery coaching. The PRC participants in the present phase of the study are also employed by this health system and are embedded within its emergency departments, MAT clinic, rural health centers, or mobile overdose response teams. These PRCs focus on providing emotional support and connection to treatment-related and community resources, and undergo relevant trainings such as cardiopulmonary resuscitation (CPR), suicide prevention (QPR; Question, Persuade, Refer), and naloxone administration. The PRC team’s manager has an existing collaborative relationship with the research team and has been involved with the project since its initial proposal and design phases.

### Intervention

The primary study intervention, as described in the study design below, involves end-user trials of a novel platform (Peer PLUS) previously developed by our research center. This platform consists of a web-based client management system for use by PRCs, and an associated mobile app to facilitate PRC-client communication, intended to be used throughout the duration of each client’s engagement with PRC services. The initial prototype of the app was developed following the 3 phases, using UCD, to ensure it reflected the needs of our health system, its PRCs, and the clients they support [32]. In the formative research phase, we consulted with SUD recovery professionals within our health system to establish an initial set of user needs, which included the ability to establish potentially urgent contact and to schedule and monitor appointments. We then assessed existing mobile apps marketed for recovery support, finding that none met these needs. Subsequently, we conducted 2 stakeholder focus groups. In the first, individuals in recovery discussed their needs in the early stages of recovery, establishing that they would value a tool that both facilitated supportive communication and connected them to additional resources. In the second focus group, which included both PRCs and clients, we used a card sorting activity to rate proposed concepts and features based on the previously identified sets of needs. Next, in the design phase, we devised requirements based on these findings, which we then implemented in a high-fidelity prototype. In the evaluation phase, we evaluated this prototype with PRCs and clients in one-on-one usability sessions where participants explored the app, performed specific tasks, rated its usability, and discussed its potential benefits. Leveraging these results, we refined the platform into a fully functional prototype to be tested in this study.

During the beta testing and pilot phases of this study, clients and their PRCs will use the app for asynchronous communication when possible over a period of up to 6 months. Clients and PRCs will be given an instructional overview of the various functions of the app (eg, sending messages, accessing and sharing resources, and setting appointments), and PRCs will send their client a sample message during this introduction, but the dyads will otherwise be instructed to use the app naturally within the context of their existing support relationship. PRCs will additionally use the client management portion of the platform for their existing tasks related to documentation in lieu of their prior workflow, which consisted of a Microsoft Excel spreadsheet. During and after this usage, participants will be surveyed and interviewed about their experience, as detailed below.

